**Figure 1 F1:**
[figure not shown]
Study design.

### Participants

Children aged between 7 and 15 years with CP will be invited to participate. Through the Cerebral Palsy Register of Norway (CPRN) we have identified 70 children with unilateral CP and 45 children with bilateral CP born in these health regions. The children must be able to use a personal computer mouse and they will be included if they understand the instructions and the intention of the computer game, regardless of IQ. Children with Gross Motor Function Classification System (GMFCS) level V (most severe CP)
[1] or who have severe visual or hearing impairments, or photosensitive epilepsy will be excluded. Participants will be recruited from the following counties: Nord- and Sør-Trøndelag (Health region Mid-Norway), Vestfold, Telemark, Aust- and Vest-Agder (Health region Southeast Norway) and from Rogaland (Health region West Norway).

### Outcome measures and assessment procedure

The primary outcome measure is the spatial span task from the Wechsler Memory Scale 3rd edition, assessing spatial working memory at four to six weeks after training (t2/t3) (Table 
1).

**Table 1 T1:** Neuropsychological tests and parental questionnaires at baseline and follow-up assessments

			**Time point**			
**Function assessed**	**Test battery**	**Subtests**	**T1**	**T2**	**T3**	**T4**
General cognitive ability	WISC-IV	Subtests included in Full IQ	X			
Attention	NEPSY II	Animal sorting	X	X	X	X
		Inhibition	X	X	X	X
		Auditory attention and response set	X	X	X	X
Executive	NEPSY II	Verbal fluency	X			
Social perception	NEPSY II	Affect recognition	X	X	X	X
Working memory	WISC-IV	Digit span	X	X	X	X
		Letter-number sequencing	X			
		Arithmetic	X	X	X	X
	WMS-III	Spatial span board	X	X	X	X
Language	NEPSY	Phonological processing	X	X	X	X
Learning/memory	NEPSY II	Memory for designs	X	X	X	X
		Memory for designs delayed	X	X	X	X
		Word list interference	X	X	X	X
		List memory	X	X	X	X
		List memory delayed	X			
		Narrative memory	X			
Visual-spatial processing	NEPSY II	Geometrical puzzles	X			
Questionnaires	BRIEF	Behavior Rating Inventory For Executive Functions	X	X	X	X
	VABS	Vineland Adaptive Behavior Scale	X		X	X
	ADHD RS	Attention Deficit Hyperactivity Disorder Rating Scale	X	X	X	X
Socioeconomic status of parents	SES	Hollingshead two factor index of social position that is based on the parent’s education and occupation	X			

Developmental NEuroPSYchological Assessment 2nd edition; IQ: Intelligence quotient; NEPSY II; SES: socio-economic status; T1: Baseline assessment; T2: Assessment after training; T3: longterm follow-up at six months post-training; WISC-IV: Wechsler Intelligence Scale for children 3rd edition.

### Neuropsychological assessment at baseline (t1)

The examination at baseline will include a full WISC- IV. Age-appropriate norms from the Scandinavian standardization will be used to calculate IQ scores. The comprehensive ‘Developmental Neuropsychological Assessment’ (NEPSY) will be applied to study memory and learning, language, attention and executive functions. At baseline the assessment lasts for approximately 3.5 hours including breaks. After completion of the baseline assessment, participants will be randomized to either training or treatment-as-usual.

### Neuropsychological assessment at follow-up (t2/t3 and t4)

To study the short-term and longterm effects of training on working memory, a training index is provided by Cogmed (http://www.pearsonassessment.com) based on the individuals training results in the computer program (’trained tasks’)
[16]. The effects of the training on non-trained working memory tasks will be assessed with the following standardized neuropsychological tests: spatial span board (WMS-III), letter-number sequencing and digit span (WISC-IV). Subtests from the NEPSY battery will also be included. At both the short-term (t2) and longterm (t3) follow-up the same battery of neuropsychological tests will be administered, lasting for approximately 1.5 hours including one break.

### Questionnaires

Parents will be asked to complete questionnaires regarding their child’s functioning in daily life (measured using the Vineland Adaptive Behaviour Scale) at baseline and at the six-month follow-up. Symptoms of attention deficit and hyperactivity (measured using the ADHD rating scale) as well as executive functions (measured using the Behaviour Rating Inventory of Executive function - BRIEF) will be administered at all time points (t1-t3). The child’s main teacher will be asked to complete the ADHD rating scale, as well as the BRIEF-teacher rating at baseline and at four to six-weeks after completing the training.

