## Methods/Design

### Objectives

The main goals of the present study are as follows: To present cognitive profiles reflecting neuropsychological functions in children with different subtypes of CP with varied aetiology. Also, to study of a computer-based training program can improve the working memory capacity of children with CP (near transfer effect), and improve learning abilities and behaviour. While learning abilities are assessed by neuropsychological learning and memory tests, behaviour will be assessed by questionnaires (the Vineland Adaptive Behaviour Scale and ADHD rating scale) given to parents and school teachers (far transfer effect). If the intervention is effective, will the beneficial effects persist over time? Assessment will include questionnaires and neuropsychological tests at six months post-training.

To present cognitive profiles reflecting neuropsychological functions in children with different subtypes of CP with varied aetiology.

To study if a computer-based training program can:

Improve the working memory capacity of children with CP (near transfer effect).

Improve learning abilities and behaviour. While learning abilities are assessed by neuropsychological learning and memory tests, behaviour will be assessed by questionnaires (the Vineland Adaptive Behaviour Scale and ADHD rating scale) given to parents and school teachers (far transfer effect).

If the intervention is effective, will the beneficial effects persist over time? Assessment will include questionnaires and neuropsychological tests at six months post-training.

This study will provide new knowledge on the effectiveness of a computer-based cognitive training program in improving the daily-life function and behavioral problems of children with CP. We hypothesize that neuropsychological deficits and impairment will be frequent in this group. Our main hypotheses are that working memory can be improved through cognitive training in children with bilateral as well as unilateral CP, the two most common CP subtypes. We also hypothesize that improved working memory will result in improved learning abilities and less symptoms of inattention.

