### Design

The study is a multicentre, clinical controlled trial applying a stepped-wedge design, as described by Brown and Lilford
[49]. The children will be examined at baseline (before the start of training - t1) and immediately after completed training (after four to six weeks - t2). According to the stepped-wedge design, group 1 will start training while the other group will wait and serve as the control. Group 2 will then start training when group 1 has completed its training (Figure 
1). This design ensures a well matched control group enabling adjustment for the natural cognitive development that occurs over time. Group 1, the first to receive the training, will also meet for the follow up after group 2 has finished the training to ensure that the researchers remain blinded to group adherence throughout the study (t3). All participants will meet for a longterm follow-up six months after completing training for each group respectively (t4). The primary endpoint will be the assessment performed at four to six weeks after training (t2 and t3).

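### The Vineland scale is never scheduled at t2, so this far-transfer outcome has no untrained comparator; the timing of the teacher forms is ambiguous

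*Protocol article*

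**What the plan says.** All references are to the protocol article.

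- **Objectives** makes behaviour a treatment outcome: "behaviour will be assessed by questionnaires (the Vineland Adaptive Behaviour Scale and ADHD rating scale) given to parents and school teachers (far transfer effect").
- **Design** sets the only controlled period: "group 1 will start training while the other group will wait and serve as the control". It continues: "Group 2 will then start training when group 1 has completed its training". The last visit comes "six months after completing training for each group respectively (t4").
- **Questionnaires** places the Vineland, completed by parents, "measured using the Vineland Adaptive Behaviour Scale) at baseline and at the six-month follow-up". Parents complete the ADHD rating scale and BRIEF at every time point. Teachers complete the ADHD rating scale "as well as the BRIEF-teacher rating at baseline and at four to six-weeks after completing the training".
- **Table 1**, in the row for the "Vineland Adaptive Behavior Scale", marks T1, T3 and T4 and leaves T2 blank. The BRIEF and ADHD rows are marked at all four visits. The footnote reads "T3: longterm follow-up at six months post-training", although the table also has a T4 column and Design makes t4 the six-month visit.
- **Statistical methods** plans a general linear model for the neuropsychological tests and the questionnaires, with group as the fixed factor.

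**The concern.** In this design the waiting group is what separates a training effect from the cognitive development expected in children aged 7 to 15. Design gives that as the reason for having it. An outcome benefits only if it is measured in both groups while one is trained and the other is not.

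The Vineland is not measured then. The planned group comparison can still be run on later Vineland scores, but it would not contrast training with no training. The change within each group from baseline would include growth. Yet Objectives promises evidence of effectiveness on daily-life function, and the dissemination plan includes a paper on effects on activities of daily living. A later analysis plan cannot repair this, because the t2 data would not exist.

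The teacher forms raise a related but weaker question, because their single follow-up is dated from the completion of training.

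**Working it through.** The plan gives no figure to reproduce here, so the check sets the schedule against training status.

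**Step 1. Training status and parent forms at each visit** (status from Design; forms from Questionnaires and Table 1):

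| Visit | Group 1 | Group 2 | Vineland, text | Vineland, Table 1 | Parent ADHD scale and BRIEF, Table 1 |
|---|---|---|---|---|---|
| t1 | untrained | untrained | yes | yes | yes |
| t2 | trained | untrained | no | no | yes |
| t3 | trained | trained | no | yes | yes |
| t4 | trained | trained | yes | yes | yes |

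Visits at which the groups differ in training status and the form is collected:

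- Vineland by the text: none.
- Vineland by Table 1: none.
- Parent ADHD rating scale and parent BRIEF: one, t2.
- Learning and memory subtests marked at T2 in Table 1 (memory for designs, immediate and delayed; word list interference; list memory): one, t2.

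The text and Table 1 disagree about T3 but agree in omitting t2. Whether the six-month visit is called t3 (footnote) or t4 (Design) changes nothing, since both groups have trained by either.

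**Step 2. Teacher forms, two readings.**

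- Literal: the follow-up is dated from each child's own training. Group 1 is rated at t1 and t2, group 2 at t1 and t3. They share no post-baseline visit.
- Loose: the phrase stands for the t2/t3 visits, as it does for the primary outcome. Both groups are then rated at t2, and the comparison is controlled.

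**Step 3. Lag between the groups' teacher ratings on the literal reading.** Inputs: training lasts 5 to 6 weeks and assessment follows 4 to 6 weeks later (Abstract). I assume that training in group 1 starts at baseline and that durations are equal in the two groups.

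- Group 1: 5 + 4 = 9 to 6 + 6 = 12 weeks from baseline.
- Group 2, starting after group 1's t2 assessment (Abstract): 9 + 9 = 18 to 12 + 12 = 24 weeks. Lag: 18 − 9 = 9 to 24 − 12 = 12 weeks.
- Group 2, starting when group 1 finishes training (Design): 5 + 9 = 14 to 6 + 12 = 18 weeks. Lag: 14 − 9 = 5 to 18 − 12 = 6 weeks.

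The lag is therefore about 5 to 12 weeks, depending on when group 2 starts.

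**Step 4. Why group 2's start matters beyond the lag.** If group 2 started as soon as group 1 finished training, and t2 came 4 to 6 weeks after that, group 2 would be 4 to 6 weeks into its own 5 to 6 week course at t2. The grid in step 1 relies on the Abstract's order, or on t2 falling immediately after group 1's training, as another sentence in Design has it.

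**The case against.** The strongest reply concerns the teacher forms. Design and the outcome section use nearly the same phrase for the primary outcome, where it plainly means t2/t3 visits that both groups attend. Taken literally throughout, it would deny spatial span a control too, which contradicts the design. This stands. A reader might infer that teacher ratings have no untrained comparator, but the document does not establish that. What remains is that only one teacher follow-up is described, in contrast to every time point for parents, and Table 1 is captioned for parental questionnaires. No sentence settles the matter.

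A second reply is that behaviour is not left without control. The parent ADHD rating scale and BRIEF are collected at t2, and the stated far-transfer hypothesis concerns learning and inattention, not adaptive behaviour. This also stands. It rules out the broader inference that far transfer as a whole, or the whole daily-living paper, rests on uncontrolled change. It does not help the Vineland, which Objectives names as a far-transfer measure and which Questionnaires makes the measure of daily function.

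A third reply is that a t2 Vineland would be rated by parents who know the allocation, since training is done at home with weekly coaching of the family. That is true, and it limits the remedy. An unblinded controlled comparison is still more informative about training than no controlled comparison.

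**Conclusion.** For the Vineland the point is firm: no visit in either schedule offers an untrained comparator, so the trial as written cannot estimate a controlled effect on that outcome. The conclusion assumes only that group 2 has trained by t3 and t4, as Design states.

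For the teacher forms the finding is ambiguous wording. Followed literally, it would leave the groups without a common follow-up, with ratings about 5 to 12 weeks apart from baseline.

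The parent ADHD rating scale, parent BRIEF and repeated learning and memory subtests have a t2 comparator, provided group 2 is still untrained at t2. The primary outcome's schedule includes t2 and does not share this gap. The documents do not support a numerical prediction of the Vineland difference between groups at t3 or t4, since durability of benefit, waning and unequal time since baseline could all affect it.

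**What to change.** 1. Collect the parent Vineland at t2 in both groups, before group 2 trains, and make group 1 versus group 2 at t2 the controlled comparison. Keep the later Vineland assessments as descriptive. State that parents are not blinded.
2. For children already past t2, or if the form cannot be added, report the Vineland as uncontrolled change and make no efficacy claim from it.
3. State that the teacher ADHD rating scale and teacher BRIEF are completed at t2 in both groups.
4. Reconcile the visit labels and schedules across the Abstract, Design, Table 1 with its footnote, the follow-up assessment section and Questionnaires. Two things need one answer: whether T3 is the visit after group 2's training or the six-month follow-up, and when group 2 starts relative to t2.

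The cost is one more parent questionnaire at a visit where parents already complete two, and a fixed date for a teacher form already planned. The Trial status section says recruitment is still under way, so children who have not yet reached t2 can still be covered.

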### Intervention

The Cogmed Robomemo™ program is designed as a computer game in which an animated robot gives different tasks to be solved by the child. During each training session the child is presented with eight different tasks. The program is adaptive in that its difficulty level increases or decreases depending on the individual child’s performance in any given task. If the child makes consecutive errors on a task the program will decrease the load of the task by reducing the number of items presented to be held in working memory. If the child successfully solves consecutive tasks the number of items presented will increase. The child will do the training at home using his or her own computer for about 30 to 45 minutes each day, five days a week for five weeks. A certified coach follows the training progress through a secure website and supervises the child by contacting the family once a week to give feedback, as well as encouragement and advice for further improvement of the results. All participating sites have certified coaches trained by Cogmed to perform this task. The coaching and assessments will be performed by other researchers to enable assessors to be blinded to group adherence (training versus no training group).

### Statistical methods

Data will be analysed using the IBM SPSS statistics software for Windows, version 19 (IBM Corp. Released 2010. IBM SPSS Statistics for Windows, Version 19.0. Armonk, NY: IBM Corp, USA) (Illinois, United States). Differences in group means for variables with a normal distribution will be compared with the Student’s *t-*test. Outcome measures not normally distributed will be analyzed using the Mann-Whitney *U* test. The Wilcoxon signed-rank test for two related samples will be used to compare scores at the two time points (baseline versus immediately after training). A univariate general linear model will be used to compute mean values for the neuropsychological tests and questionnaires adjusted for gender and SES, with the group as the fixed factor and sex and the SES as covariates. A full data analysis plan will be drafted before unmasking group adherence.

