### Estimation of sample size

The aim of the present study is to demonstrate a clinically significant effect of the training on working memory, and we defined this as a 10% score increase on the main outcome measure, the spatial span from the WMS-III, in those children who had performed the training as compared with those in the control group. In order to estimate the sample size needed to meet this aim, we applied results (mean and SD) from one of our previous intervention studies in adolescents born with extremely low birth weights (ELBW; birth weight (BW) of less than 1000 g), of whom two participants had CP (Løhaugen *et al.*[18]). Using these figures, we estimated (sample power 3) that we would need to recruit 100 participants in order to show a 10% improvement in spatial span following training, with an 80% power and a two-tailed alpha of 0.05. In order to allow for a dropout rate of 15%, we decided to include 115 participants.

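### The observed distribution decides which test is used for the primary outcome, and neither test is ranked against the adjusted model; one mean-based analysis should be named as primary

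*Protocol article*

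**What the plan says.** All references are to the protocol article.

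- **Primary outcome** (Outcome measures and assessment procedure): "The primary outcome measure is the spatial span task from the Wechsler Memory Scale 3rd edition", assessed four to six weeks after training (t2/t3). The section does not say whether raw or scaled scores are used.
- **Group comparison** (Statistical methods): "Differences in group means for variables with a normal distribution will be compared with the" Student t-test. For the rest: "Outcome measures not normally distributed will be analyzed using the Mann-Whitney" U test. No criterion for normality is given, and no outcome is exempt.
- **Adjusted model** (same section): "A univariate general linear model will be used to compute mean values for the neuropsychological tests and questionnaires adjusted for gender and SES". Group is the fixed factor; sex and SES are covariates. The model carries no condition on the distribution and is not ranked against the two tests.
- **Later plan** (same section): "A full data analysis plan will be drafted before unmasking group adherence".
- **Target effect** (Estimation of sample size): "we defined this as a 10% score increase on the main outcome measure, the spatial span from the WMS-III", relative to the control group. For the inputs, "we applied results (mean and SD) from one of our previous intervention studies"; neither value is reported. The calculation gives 100 participants "with an 80% power and a two-tailed alpha of 0.05", raised to 115 for dropout.

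The section also names a Wilcoxon signed-rank test. It compares two time points in the same children, so it does not compete for the between-group question.

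**The concern.** Two things are fixed badly for the outcome that decides the trial.

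First, the trial's own outcome data choose the between-group test, by a criterion nobody has stated. The two tests do not address the same quantity. The t-test compares means. Mann-Whitney compares ranks and returns no difference in mean score. The trial is sized on a percentage gain in a score, worked out from a mean and an SD, which is a statement about means. If the rule selects the rank test, the deciding p-value and the design target refer to different quantities.

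Second, the adjusted model gives another group comparison of the same scores, and the text does not say which result settles the hypothesis. At stake is an unfixed target of estimation and some freedom to choose between two results.

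**Working it through.** **1. The plan's own figure.** The 100 participants cannot be reproduced forwards, because mean and SD are not reported. Solved backwards, assuming 1:1 allocation (50 per group):

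- Standardised effect, normal approximation: d = (1.960 + 0.842) × √(2/50) = 0.560. The t-based value is 0.566.
- A 10% gain equals d × SD, so SD/mean = 0.10/0.560 = 0.178, or 0.10/0.566 = 0.177.

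The sizing is therefore coherent as a comparison of two means if the SD is nearly 18% of the mean.

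**2. Rank test on normal scores.** The efficiency of Mann-Whitney relative to the t-test is 3/π = 0.955.

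- Effective size per group: 50 × 0.955 = 47.7. Power = Φ(0.560 × √(47.7/2) − 1.960) = 78%.
- Participants for 80% power: 100/0.955 = 104.7, so 105.

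**3. Simulation.** 3,000 trials per setting, 50 per group. Scores are normal with SD/mean 0.177, rounded to whole points. SES is assumed to explain 5% of the variance. Whole-number scoring and the SD in points are assumptions, so the SD is varied. A trial counts as non-normal if either group is rejected at 0.05. The Lilliefors column uses 1,000 trials. The rule applies t-test or Mann-Whitney according to Shapiro-Wilk.

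| SD (points) | Non-normal, Shapiro-Wilk | Non-normal, Lilliefors | Type I, rule alone | Type I, better of rule and adjusted model |
|---|---|---|---|---|
| 1 | 100% | 100% | 5.2% | 6.2% |
| 1.5 | 97% | 100% | 4.7% | 6.3% |
| 2 | 60% | 95% | 5.6% | 6.6% |
| 2.5 | 35% | 81% | 4.7% | 6.0% |
| 3 | 24% | 63% | 5.6% | 7.1% |
| 4 | 17% | 41% | 5.1% | 6.3% |

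The simulation standard error at 5% is √(0.05 × 0.95/3000) = 0.4 points, so the rule alone cannot be told apart from 5%.

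**4. Power at the planned effect, same simulation.** t-test 76–79%, Mann-Whitney 75–77%, the rule 75–78%, adjusted model 77–80%. All tend to fall a little short of 80% because rounding adds variance and the effect was set at d = 0.560.

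**5. Non-normal scores.** In a separate simulation (4,000 trials per scenario, SES explaining more of the variance), the linear model had 83% power against 86% for Mann-Whitney with strongly skewed scores, and 82% against 78% with near-normal scores.

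**The case against.** The strongest reply is that the protocol promises a full analysis plan before group allocation is unmasked. Naming a primary analysis and a normality criterion is ordinary content for that plan, and a plan fixed before unmasking would largely remove the choice between results. This stands as far as it goes: the plan is not shown, and it may rank the analyses. But the objection here is to a rule already written down, which the promise does not withdraw. A plan that elaborates the rule would keep the mismatch with the sizing target.

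Four stronger readings are tempting, and the documents do not support them.

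- *The rank test will usually be chosen.* A reader might infer this from the coarseness of a span score. No section states that the score takes whole values, how it is scaled or what its SD is, and no formal normality test is named. With Shapiro-Wilk at SD 2.5, the t-test would be the more frequent choice.
- *The plan cannot estimate the 10% gain.* That is true of Mann-Whitney but not of the plan. The linear model yields adjusted group means whatever the distribution, so a mean difference is available. The model is simply not named as primary.
- *Three p-values compete for one hypothesis.* The t-test and Mann-Whitney are alternatives, so at most two results exist per outcome. The simulated error for the best of three (6.5–7.7%) describes a procedure that the protocol does not set out.
- *The switching rule itself inflates type I error.* It does not, as the simulation shows.

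It is also fair to say that the rank test has a small power advantage under strong skew, so the switch is not without benefit.

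**Conclusion.** The point holds in a limited form. For spatial span at t2/t3, the deciding test depends on the observed distribution by an unstated criterion, and its standing against the adjusted model is not settled. When the rule selects Mann-Whitney, the deciding test does not estimate the quantity on which the trial was sized.

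The numerical effect is small. Error stays near 5% under the rule alone and rises to about 6–7% only if the better of two results is reported. Power differs by a few points between the options. These figures assume 50 per group, rounded normal scores and a weak SES effect. The selection rate of 17% to 100% rests wholly on an assumed score scale and normality check. The main reason to act is that the primary analysis should match the design target and be fixed in advance. This should be corrected, but it does not undermine the trial.

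**What to change.** For the primary outcome, replace the distribution rule in Statistical methods with one named analysis, whatever the distribution. This is the between-group difference in mean spatial span, with a 95% CI, from the general linear model already planned, preferably with the t1 spatial span score added as a covariate, since it is collected anyway. State that Mann-Whitney is a labelled sensitivity analysis and cannot replace the primary result. Carry the same wording into the promised analysis plan.

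The change takes about one sentence and leaves the target of 100 evaluable participants as it is. The drawback is slightly less power than the rank test if scores prove strongly skewed: 86% − 83% = 3 points in the skewed scenario above.

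### The pre-post signed-rank test uses no control data, is not limited to description, and is the only listed method that explicitly uses the baseline score

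*Protocol article*

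**What the plan says.** All references are to the protocol article; t1 to t4 are used as its Design section defines them.

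- **Statistical methods** lists four procedures. Two compare groups without mention of baseline: "Differences in group means for variables with a normal distribution will be compared with the Student’s" t-test, and "Outcome measures not normally distributed will be analyzed using the Mann-Whitney" U test. The third is a general linear model, "with the group as the fixed factor and sex and the SES as covariates". The fourth is within-person: "The Wilcoxon signed-rank test for two related samples will be used to compare scores at the two time points (baseline versus immediately after training".
- The section does not say in which group or for which outcome the signed-rank test is run, or whether its result counts as evidence of effect. It names no procedure as primary. It says that a full analysis plan will be written before group membership is unmasked.
- **Design** gives the purpose of the control group: "This design ensures a well matched control group enabling adjustment for the natural cognitive development that occurs over time". Group 2 waits while group 1 trains, then trains itself. On timing: "The primary endpoint will be the assessment performed at four to six weeks after training (t2 and t3".
- **Estimation of sample size** defines the effect as a 10% higher spatial span score "in those children who had performed the training as compared with those in the control group".
- **Table 1** repeats spatial span, digit span and most other tests at all four visits.

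**The concern.** The trial has a randomised waiting control so that change from training can be told apart from change that would happen anyway. A paired baseline-to-post test does not draw on that control. Children aged 7 to 15 take the same tests repeatedly, so scores may rise through familiarity and growth even if training does nothing.

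The article's questions are about improvement: whether working memory, learning and behaviour get better. Of the four listed procedures, only the signed-rank test is expressly about change from baseline. A reader asking whether scores improved is led to the one method that cannot say why they did. At stake is a claim of training effect, on spatial span or any other repeated outcome, that practice or maturation could explain.

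**Working it through.** **1. Which comparison has an untrained control?**

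| Comparison | Children | Untrained concurrent control used? |
|---|---|---|
| t1 to t2, paired | group 1 | no, although group 2 is available |
| t1 to t3, paired | group 2 | no; group 1 has already trained, and the interval includes an extra test session |
| group 1 v group 2 at t2 | both | yes |

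Only the last comparison matches the purpose given under Design and the effect defined under Estimation of sample size.

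**2. Inputs.** The article gives no rate for this point, so there is no figure of its own to reproduce.
- Children per group: 100 are required, so 50 per group if allocation is 1:1 (assumed; the ratio is not stated). With 115 recruited and 15% dropout, 115 × 0.85 = 97.75, or about 49 per group.
- Two-sided alpha: 0.05, from Estimation of sample size.
- Retest gain g, in SD units, equal in both groups, with no training effect: **assumed** 0.1, 0.2 and 0.3.
- Correlation r between baseline and follow-up: **assumed** 0.5, 0.7 and 0.8.

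**3. Paired-t approximation to the signed-rank test, n = 49.** The SD of the change is √(2(1 − r)), and the noncentrality is g·√n / √(2(1 − r)). For g = 0.2 and r = 0.5 the SD of change is 1.00 and the noncentrality is 0.2 × 7 / 1.00 = 1.40, giving 28% rejection. For g = 0.2 and r = 0.8 the SD of change is 0.632 and the noncentrality is 1.4 / 0.632 = 2.21, giving 58%.

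**4. Simulation of the signed-rank test itself, n = 50, 2,000 runs per cell.**

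| g (SD) | Paired t, n = 49 (r = 0.5 / 0.7 / 0.8) | Signed-rank, n = 50 (r = 0.5 / 0.7 / 0.8) | Mann-Whitney or t-test, 50 v 50, same visit |
|---|---|---|---|
| 0 | 5 / 5 / 5% | 5 / 5 / 4% | 4-6% |
| 0.1 | 10.5 / 14 / 19% | 11 / 15 / 19% | about 5% |
| 0.2 | 28 / 43 / 58% | 26 / 43 / 56% | 4-6% |
| 0.3 | 54 / 76 / 90% | 54 / 75 / 90% | 5-6% |

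The two methods agree to within about two percentage points. Taken together they give about 11-19%, 26-58% and 54-90%.

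**5. Pooling.** If both groups' pre-post data were pooled (n = 100), the simulated signed-rank rates would be 15-33%, 49-87% and 82-99.5%. The article does not say that they would be pooled.

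**6. What adding baseline does.** In a linear model with the baseline score as covariate, residual variance falls to about 1 − r² of its unadjusted value: 0.75 at r = 0.5, 0.51 at r = 0.7 and 0.36 at r = 0.8. The model as written names only sex and SES and does not state this gain.

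**The case against.** The strongest reply is that the article does plan valid tests. Three of its four procedures compare groups, the effect is defined against the control group, and randomisation balances expected practice and maturation at a same-visit comparison. The simulation supports this: the unadjusted between-group tests hold about 5% whatever the retest gain. This stands, and it rules out several stronger readings that a reader might infer.

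- *That the plan will attribute practice and maturation to training.* That would require the signed-rank test to be the efficacy test. No section gives it that role.
- *That every efficacy conclusion carries a false-positive risk above 5%.* Only a conclusion resting on the signed-rank test does.
- *That the two groups' separate pre-post p-values will be compared.* This is a known fallacy, but the article does not propose it.

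It is also fair that, if scores truly rise by 0.2 SD, rejecting no change is a correct rejection. The error lies in attributing the rise to training. Age-normed scores would remove part of the maturation, but not practice; the article does not say which type of spatial span score is used.

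Finally, the ranking of tests can be left to the later analysis plan, and its absence here is not the complaint. What remains is in the stated text: a control-free test listed on equal footing with the others, and a between-group model whose stated covariates omit baseline.

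**Conclusion.** The point holds in a limited form. The signed-rank comparison is listed without being confined to description, makes no use of the control group, and is the only listed method that explicitly uses baseline. Any training-effect conclusion resting on it cannot be separated from retest practice or maturation.

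The size depends on quantities that the article does not give. Even the smallest gain considered, 0.1 SD, at least doubles the nominal 5%. The result assumes normally distributed scores, about 50 children in the group tested, and the stated ranges of gain and correlation. The planned between-group tests are not affected. The point should be settled before unmasking, but it does not invalidate the trial.

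**What to change.** In the analysis plan that is to be written before unmasking:

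1. State that the efficacy analysis is the comparison of group 1 with group 2 at t2, while group 2 is still untrained.
2. Add the baseline score of the same outcome to the planned general linear model, alongside sex and SES. Do this for spatial span and for every other outcome measured at both t1 and t2. The Vineland scale has to be exempted: neither Table 1 nor the Questionnaires section has it at t2.
3. Report pre-post changes for both groups, including group 2's change to t3, as descriptive only, preferably as means with confidence intervals side by side.
4. State that the signed-rank test is not used as evidence of a training effect.

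The cost is wording. Table 1 already schedules the baseline scores, so no visit, test or participant is added. At the assumed correlations, the baseline covariate should also sharpen the comparison.
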